### Analysis

#### Quantitative analysis

Analyses will be undertaken on an intention to treat. Intention to treat analysis is defined in this study as an a priori plan to analyse the data according to the groups to which the subjects were randomised regardless of the treatment they received.

Fall rates for each group will be expressed as number of bedside falls per 1,000 bed days. The number of bedside falls per patient will be compared between groups using Poisson regression allowing for over dispersion, with length of stay in days as an offset. Crude models containing intervention group only will be fitted initially, whilst additional models will adjust for the effects of age, MMSE and mobility/transfer scores. Interactions between each of these three variables and treatment group with respect to our primary and secondary outcome measures will also be examined, with covariates dichotomised where necessary. For other secondary outcome measures, groups will be compared using the independent samples t-test for continuous outcomes (or Mann-Whitney U test if assumptions for using the t-test are not satisfied following appropriate transformations of the data) and the chi-square test for binary/categorical outcomes. The rate of falls in the trial wards in the 12 months prior to the trial commencing will be compared with the rate of falls in the control arm during the trial using Poisson regression, allowing for overdispersion as appropriate. A significance level of p < 0.05 will be used for all analyses.

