### Secondary research hypotheses

1. There is a beneficial effect of pressure sensors upon health outcomes (transfer and mobility, fear of falling, quality of life, length of hospital stay and residential status on discharge) in hospitalised older people.

2. That the intervention above is cost-effective compared to usual care from a secondary care NHS perspective.

3. That there are groups of patients in whom the health or economic benefits from the intervention are greatest.

4. That the sensor system is acceptable to staff and patients and practical for use in an acute hospital setting.

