### Outcome measures

#### Definition of primary and secondary outcome measures

The primary outcome measure is the number of bedside in-patient falls per 1,000 bed days from time of randomisation until the participant is discharged from the ward.

A bedside fall is defined as an unexpected event in which the participant comes to rest on the ground, floor or lower level in the area around the bedside, with the bedside being defined as the area encompassed by the curtained area surrounding the bed. For participants in side rooms, the bedside is defined as the area of the room.

The secondary outcome measures are:

a. Number of injurious in-patient falls per 1,000 bed days, defined as falls resulting in abrasion, bruise, swelling, cut, laceration, dislocation, fracture or muscle sprain or strain.

b. Length of hospital stay.

c. Residential status on discharge.

d. Transfer/mobility score and activities of daily living, measured using the Barthel Index [26].

e. Fear of falling, measured using the Modified Falls Efficacy Scale (mFES) [27] to ascertain any differential fear of falling in the two participant groups due to an increased awareness of a potential for a fall, or a greater sense of safety arising from sensor use.

f. Health related quality of life, measured using the EUROQOL EQ-5D [28].

g. Participant and staff experience of using bed and chair sensors. This sub-study will be reported separately.

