##### (a) baseline data

The baseline data collected at recruitment originates from face to face interview between researcher and patient, the patient's medical and nursing notes, and/or carer.

Baseline data includes:

a. Demographic and residential details, reason for admission, time since admission.

b. Any previous history of falls, and any resulting fractures.

c. Mobility and transfer before the illness that precipitated admission, and at the time of recruitment (measured by the Barthel ADL index).

d. 30 point Mini Mental Stare examination (MMSE).

e. Health related quality of life measured using the EuroQol EQ-5D.

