##### (b) follow up data

Follow up data are collected one day prior or on the day of discharge.

Follow up data includes:

a. Falls, ascertained from hospital incident reporting forms. The use of these incident forms in NUH to record falls is mandatory and enforced by clinical governance processes. Members of the research team collect copies of hospital incident reporting forms from participating wards. Data such as fall event, time, and place, injuries sustained and subsequent actions taken are recorded. Where a medical opinion has been requested, the outcome is recorded, together with any investigations requested. In addition, aggregated, anonymzed data on falls will be collected from hospital incident reporting forms for the trial wards for the 12 month period prior to the trial commencing. The rate of falls in the period prior to the trial commencing will be compared with the control arm rate of falls during the trial to explore whether the use of sensors increases the rate of falls in the control arm.

b. Transfer/mobility and activities of daily living (Barthel ADL). This information is ascertained from the participant or carer, and/or their medical and nursing notes.

c. Quality of life (EuroQol EQ-5D) ascertained by participant interview. Where a participant is unable to participate in an interview, health related quality of life is ascertained from the carer and named nurse.

d. Fear of falling (mFES), ascertained by participant interview. Where a participant is unable to take part in an interview due to poor cognitive ability, this assessment is coded appropriately and excluded from analysis.

e. Mini Mental State Examination (MMSE), through participant interview. The baseline assessment does not account for any acute delirium secondary to the patient's condition on hospitalization, which may improve with treatment. The change in delirium may have an effect on the risk of falling.

f. Length of stay and residential status on discharge, ascertained from medical records.

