### Withdrawals

Participants are free to withdraw from the trial at any stage. Participants, who decide to withdraw once recruited to the study, if allocated to a sensor, will have the sensor removed and further data collection from that point stopped. Participants, if allocated to a sensor, in whom it is deemed are at risk of harm resulting from the sensor equipment (for example in cases of confusion where the participant mis-handles the sensor equipment), will have the sensor removed and further data collection from that point stopped.

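### The primary model's offset is length of stay, which is not tied to the randomisation-to-ward-discharge window in which bedside falls are counted

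*Protocol article*

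**What the plan says.** Four parts of the protocol article bear on the exposure in the primary model.

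- **Outcome definition (Definition of primary and secondary outcome measures).** The primary outcome is a rate of bedside falls "per 1,000 bed days from time of randomisation until the participant is discharged from the ward".
- **Model (Quantitative analysis).** The per-patient count is compared between groups "using Poisson regression allowing for over dispersion, with length of stay in days as an offset". No start or end date is given for that stay.
- **What length of stay means elsewhere.** Secondary outcome b is "Length of hospital stay". The follow-up data list gives its source: "Length of stay and residential status on discharge, ascertained from medical records". The sample size section uses an undated ward average of 19 days.
- **When follow-up starts and stops.** The baseline data include "Demographic and residential details, reason for admission, time since admission", so recruitment can follow admission. Under Withdrawals, a sensor-arm participant judged at risk of harm from the equipment "will have the sensor removed and further data collection from that point stopped". The same applies to sensor-arm participants who choose to withdraw.

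The secondary hypotheses also expect sensors to benefit "length of hospital stay and residential status on discharge", so stay is itself something the intervention may change.

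**The concern.** An offset should measure the time during which the counted events could have been recorded. Here the numerator opens at randomisation and closes at ward discharge, or earlier if data collection stops. A hospital stay opens at admission and closes at hospital discharge. A statistician following the analysis section to the letter would divide by days before randomisation, days after leaving the trial ward, and possibly days after ascertainment has ended.

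Three things are at stake:

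- the absolute rate per 1,000 bed days, which is the declared primary measure;
- the comparison of the control-arm rate with the wards' rate in the 12 months before the trial, which is meant to detect harm to controls;
- under particular conditions, the rate ratio itself.

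**Working it through.** **Inputs from the protocol article.** Control rate 8.0 per 1,000 bed days, average stay 19 days, target rate ratio 0.65, overdispersion 1.5, 80% power, alpha 0.05, 905 per arm (all Sample size).

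**Inputs assumed.** The article gives neither the gap *d* from admission to randomisation, nor the change in stay due to sensors, nor the share *w* of sensor participants whose data collection stops early. Ranges are shown instead.

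**1. The plan's own figure.** Falls per patient: 0.008 × 19 = 0.152 (stated as 0.15). The Poisson-regression sample size formula with two-sided alpha is

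n per arm = 0.5 × 1.5 × [1.96 × 2 + 0.8416 × √(2 + 2/0.65)]² / (μ × (ln 0.65)²).

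It gives 900 at μ = 0.152, 905 at 0.151 and 912 at 0.150. The stated 905 reproduces. Planning thus treats the 19 days as exposure days, without saying when they start.

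**2. Pre-randomisation days in the denominator.** Reported rate = true rate × (19 − d)/19.

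- d = 2: 8.0 × 17/19 = 7.16, understated by 1 − 17/19 = 10.5%.
- d = 5: 8.0 × 14/19 = 5.89, understated by 1 − 14/19 = 26.3%.

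If both arms have the same stay, the factor cancels in the ratio: 1.00 stays 1.00 and 0.65 stays 0.65.

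The factor does not cancel in the before-and-during comparison if the pre-trial rate is calculated over all ward bed days. The control-arm rate would then look too low, which is falsely reassuring.

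**3. Sensors shorten the stay after randomisation.** With post-randomisation stays Pc (control) and Ps (sensor),

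reported ratio = true ratio × [Ps/(Ps + d)] / [Pc/(Pc + d)].

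Take d = 5, so Pc = 14:

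- 2 days shorter: (12/17)/(14/19) = 0.958; a true 0.65 reads 0.623.
- 4 days shorter: (10/15)/(14/19) = 0.905; a true 0.65 reads 0.588.

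With d = 2, the corresponding null values are milder, 0.986 and 0.969.

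**4. Sensor-arm participants stop halfway but keep their full stay as exposure.** Reported ratio = true ratio × (1 − 0.5w). The rejection probability under the null uses variance (1.5/905) × [1/0.152 + 1/(0.152 × ratio)] for the log ratio.

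| Share stopped, w | True 1.00 reads | True 0.65 reads | Two-sided type I error |
|---|---|---|---|
| 5% | 0.975 | 0.634 | 5.3% |
| 10% | 0.95 | 0.617 | 6.4% |
| 20% | 0.90 | 0.585 | 10.7% |

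**The case against.** The best defence is that the outcome definition already fixes the window. It attaches the period from randomisation to ward discharge to the whole rate, and the analysis section restates the rate just before naming the offset. On that reading, length of stay is shorthand for those same bed days. The sample size section lends support, because it uses length of stay as fall exposure on the wards. This reading is possible. However, the article never states it, and where length of stay is an outcome it is hospital stay. Nor can the point simply be left to an analysis plan, because the protocol itself fixes the offset.

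The second objection concerns the stopped participants. If data collection ends, a stay recorded at discharge may not exist for them, so step 4 need not occur. That stands, and step 4 is therefore conditional. But these participants remain in the intention-to-treat groups, and the article then states no exposure for them at all.

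Four stronger readings are tempting but are not supported:

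- **That the ratio is biased as a matter of course.** Pre-randomisation days alone do not bias it when stays are similar.
- **That the null ratio falls to 0.85–0.94.** This needs 8–12% of the sensor arm stopped after 10–50% of their stay, doubled fall risk in confused patients, about 40% of patients confused, and full stay kept as exposure. The article gives a doubled risk only for dementia in general. It supplies none of the other inputs.
- **That early clustering of falls demonstrates the error.** A 10% shorter stay with unchanged daily risk can give a count ratio of about 0.92 and a rate ratio of 1.025. That rate ratio arises with the correct, post-randomisation denominator; with full stay it is about 1.014. It therefore does not show this fault, and it runs against the sensor.
- **That the wrong model is specified because the offset is not called a logarithm.** Naming the exposure as the offset is common shorthand.

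**Conclusion.** The point holds as a mismatch of windows in the primary analysis. Taken literally, the offset covers days on which no fall can be counted.

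The most direct effect is on the absolute rates: an understatement of 11–26% if randomisation is 2–5 days into a 19-day stay, with a possible knock-on to the comparison with the pre-trial ward rate.

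The rate ratio moves towards the sensor only under further conditions. One is a shorter stay with sensors (a true 1.00 reads 0.958 to 0.905 with a 5-day gap and 2 to 4 days saved). The other is full stay retained after early stopping (0.975 to 0.90 for 5% to 20% stopped halfway). All of these sizes rest on assumed inputs, so the true size is unknown. Only the harm-related stop is certain to be confined to the sensor arm; the provision on voluntary withdrawal can be read as covering either arm.

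**What to change.** In Quantitative analysis, define the offset as the log of days from randomisation to the earliest of trial-ward discharge, death or end of fall ascertainment. Keep hospital length of stay only as secondary outcome b. Reconcile the outcome definition, the Withdrawals section and the analysis section, so that each says the same about when fall counting ends.

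This aligns numerator and denominator. It does not remove the selection that arises when ascertainment stops only in the sensor arm. Continuing to collect falls from incident forms, where consent allows, would address that, and it needs a separate decision.

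A supportive model of falls per participant without an offset is optional, since the rate is the declared primary outcome.

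The cost is a change of wording. The randomisation system should hold the randomisation date, and stay is already taken from the medical records, where the ward discharge date should also be found. The wording should be settled before unblinded analysis, so that the denominator is not chosen after results under both are known.

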## Background

Falls in hospitals are common, ranging from 3 to 14 for every 1,000 bed days [1]. Over 200,000 falls were reported to the National Patient Safety Agency's (NPSA) National Reporting and Learning System (NRLS) in the 12 months from September 2005 to August 2006, with falls data being reported from 98% of organisations providing in-patient services [2]. In-patient falls result in injury and anxiety to patients and large costs to NHS organisations, including the costs of treating injuries, increased hospital stay, complaints and litigation [3-5].

Elderly in-patients are at particular risk of falling with the incidence of falls being almost triple that for community-dwelling older people [6]. Several factors contribute to this including; age, a history of falling, impaired mobility and special toileting needs. People with dementia are more likely than those without it to require hospital admission, and are at least twice as likely to fall [7-9]. Up to 30% of in-patient falls occur during the first 48 hours of the patients' admission and 75% of in-patient falls occur in the first two weeks of hospital stay [7,10,11].

Our hospital audit data are consistent with published data [2] and has shown that more than half (53%) of all in-patient falls in elderly people in acute care settings occurred at the bedside, during transfers or whilst getting up to go to the toilet. In the majority of cases these falls were unwitnessed. Where patients had been advised to call for assistance they were often reluctant to ask for help as they "did "not want to bother the nurses" or were unable to do so because of cognitive impairment.

Prevention of falls is a priority for NHS policy makers and practitioners. The Healthcare Commission has used falls prevention as a focus for inspecting compliance under patient safety [12]. Despite our increasing knowledge of the aetiology and epidemiology of falls, there is a dearth of evidence for effective falls prevention in hospitals [13-15]. There is good evidence for falls prevention in the community dwelling elderly [16-18], but these findings are unlikely to generalise to the acute hospital setting.

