### Setting

Five acute older persons' care wards at Nottingham University Hospitals NHS Trust (NUH).

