### Sample size

Based on data obtained from our wards during 2005, we anticipate a rate of bedside falls of 8.0 per 1,000 bed days in the control group, assuming that 53% of all falls occur at the bedside and that the average length of stay is 19 days (mean number of falls per patient = 0.15). To detect a 35% reduction in the rate of bedside falls among the intervention group, assuming 80% power, alpha = 0.05 and an over dispersion parameter of 1.5 (to allow for non-independence of falls within individuals), 905 participants are required in each arm of the trial.

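### The plan does not say whether the crude or the adjusted model carries the primary inference, and the adjusted model omits previous falls; one prespecified adjusted model would be modestly better.

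*Protocol article*

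**What the plan says.** The primary outcome is compared by Poisson regression allowing for overdispersion, with length of stay as offset. On covariates, Quantitative analysis says: "Crude models containing intervention group only will be fitted initially, whilst additional models will adjust for the effects of age, MMSE and mobility/transfer scores". The same section applies p < 0.05 to every analysis. It gives the order of fitting but not which model decides the trial.

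On risk factors, the Background lists "age, a history of falling, impaired mobility and special toileting needs". Of these, age and mobility enter the adjusted model and falling history does not. It is nevertheless collected; the baseline list includes "Any previous history of falls, and any resulting fractures".

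The Setting is "Five acute older persons' care wards". Randomisation describes permuted blocks of varying size and no stratification factor. Table 1 shows MMSE and Barthel at both baseline and discharge, and the baseline list takes mobility both before the illness and at recruitment. The analysis text does not say which values are the covariates.

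**The concern.** Two things are at stake.

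- **Choice of model.** Two analyses of one primary outcome, each tested at 0.05 and neither ranked, allow the conclusion to rest on whichever is significant. That raises the false-positive rate somewhat above 5%.
- **Precision.** Part of the variation in falls between patients can be predicted at baseline. A model that uses this information has a smaller standard error with no added patients. Previous falls is the clearest omission, since the document itself calls it a contributing factor and already records it.

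The question is how large these effects are when a patient has on average only about one eighth of a fall.

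**Working it through.** **Inputs (Sample size section).** Control rate: "we anticipate a rate of bedside falls of 8.0 per 1,000 bed days in the control group". Exposure: "the average length of stay is 19 days (mean number of falls per patient = 0.15"; unrounded, 8.0 × 19/1,000 = 0.152. Effect: "To detect a 35% reduction in the rate of bedside falls among the intervention group", so RR = 0.65 and |ln RR| = 0.4308. Also "assuming 80% power, alpha = 0.05 and an over dispersion parameter of 1.5". Target: 905 per arm.

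**1. The plan's own figure.** The Signorini formula for Poisson regression, two-sided, is

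n per arm = φ(1.96·√4 + 0.8416·√(2 + 2/RR))² / (2·μ₀·(ln RR)²).

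With φ = 1.5 and μ₀ = 0.152: 1.5 × (3.920 + 1.896)² / (2 × 0.152 × 0.1856) ≈ 899.5. With μ₀ = 0.15 it is 911.5. So 905 reproduces, and power at 905 is 80.2%.

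**2. A second formula.** The log-rate Wald calculation gives SE = √(1.5 × (1/0.152 + 1/0.0988)/905) = 0.1664. Power = Φ(0.4308/0.1664 − 1.96) = 73.5%. Simulated crude quasi-Poisson fits at 905 per arm rejected in about 73 to 76% of trials, nearer this value.

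**3. What adjustment can gain.** Under a log link the rate ratio is collapsible. The variance of its log therefore falls by about R² = μ·CV²/φ, where μ = (0.152 + 0.0988)/2 = 0.1254 and CV² is the squared coefficient of variation of the covariate-predicted rates. The documents do not give the strength of previous falls or ward, so these scenarios are assumptions:

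| Previous fallers, their RR, ward CV | CV² | Remaining φ | R² | Power, Wald | Power, Signorini |
|---|---|---|---|---|---|
| No adjustment | 0 | 1.500 | 0 | 73.5% | 80.2% |
| 30%, 1.5, 0.1 | 0.05 | 1.494 | 0.4% | 73.7% | 80.4% |
| 40%, 2, 0.2 | 0.17 | 1.479 | 1.4% | 74.1% | 80.7% |
| 50%, 3, 0.3 | 0.36 | 1.455 | 3.0% | 74.8% | 81.3% |
| 50%, 4, 0.5 (extreme) | 0.70 | 1.412 | 5.9% | 76.1% | 82.4% |

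Example, second scenario: 1.5 − 0.1254 × 0.1673 = 1.479.

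To go from 73.5% to 80% by adjustment alone, φ must fall to 1.28. That needs R² = 14.6% and CV² of about 1.74, some 2.5 times the extreme row (1.74/0.70).

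**4. Simulation of the gain.** Gamma frailty, φ about 1.5, 905 per arm, 1,500 replicates, adjusting for previous falls and ward:

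- Second scenario: SD of the log rate ratio 0.1714 crude, 0.1702 adjusted (down 0.7%); rejection 75.3% and 76.8%.
- Third scenario: SD 0.1651 and 0.1629 (down 1.3%); rejection 75.1% and 78.7%.

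Part of the rise in rejection is not real precision. In the second scenario the estimated dispersion fell from 1.50 to 1.40, about 6.7%, while the empirical variance fell only 1 − (0.1702/0.1714)² ≈ 1.4%. The model-based standard error of the adjusted fit is then too small. Null rejection was 6.4% crude and 6.6% adjusted in the second scenario, and 5.1% and 6.0% in the third (Monte Carlo SE √(0.05 × 0.95/1,500) ≈ 0.6 points).

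With robust standard errors and covariate CV² of 0.2, 0.5 and 1.0 (3,000 replicates), power rose by about 1, 2 and 3 points. Over all simulated settings the gain was about 1 to 4 points and the SD fell by 0.2 to 2.6%.

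**5. Type I error if either model may count.** In the 3,000-replicate simulations the crude model alone rejected in 4.7 to 5.1% of null trials. Counting either model gave 5.9%, 6.6% and 7.7% with quasi-Poisson standard errors and 5.6 to 6.8% with robust ones. Further simulations with robust standard errors gave about 5 to 6%.

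**The case against.** The other side has a good case on several points.

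- **The crude comparison is valid.** Randomisation protects it. Fitting it first and calling the adjusted models additional can be read as a crude main analysis with prespecified support. Labelling the primary model is often left to a statistical analysis plan, which is not shown. This stands, and if that plan already ranks the models, only one confirming sentence is needed. The article as written still names two tests of one outcome at the same level without ranking them.
- **A reader might infer that adjustment would recover much of a power loss.** The documents do not support this. They state 80% power, and 905 reproduces at that level. Even on the Wald figure, restoring 80% needs covariates far stronger than the extreme scenario. At 0.125 falls per patient, most of the variance is Poisson noise that covariates cannot remove.
- **A reader might infer that leaving out ward is an error.** No stratification by ward is described and no ward differences in fall rates are reported. The overdispersion of 1.5 is justified by repeated falls within individuals. Ward is an optional addition.
- **A reader might infer that discharge MMSE or Barthel will be adjusted for.** The text never says so, and using the same variables for subgroup interactions fits baseline values. Inserting the word baseline settles it.
- **The gains are measured against the crude model.** Compared with the planned adjusted model, adding previous falls would probably bring less. This also stands.

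**Conclusion.** The point holds as a modest improvement to a valid plan. The article leaves the primary inference open between two models, and its adjusted model omits a risk factor that the document names and records. One prespecified adjusted model would gain about 1 to 4 power points over the crude model in simulation (0.2 to 2.5 by formula for previous falls and ward). It would also remove a false-positive rate of about 5 to 6%, reaching 6.8% with stronger covariates, that arises if either model may count.

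These sizes rest on assumed covariate strength, gamma-distributed patient risk with dispersion near 1.5, and robust standard errors for the type I figures. The 905 per arm is not shown to be wrong. The gap between 80.2% and 73.5% reflects the choice of formula, and adjustment would close only a small part of it.

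**What to change.** Name one primary analysis before allocation is revealed to the analysts:

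- An overdispersed Poisson model with the length-of-stay offset, containing arm and the baseline values of age, MMSE, mobility/transfer score at recruitment, and previous falls. Ward may be added as a fixed effect.
- Continuous covariates kept continuous in this model; the dichotomising that the plan allows belongs to the interaction analyses.
- Robust standard errors, or a stated check of the dispersion estimate, because adjustment can lower the estimated dispersion by more than the true variance.
- The crude rate ratio reported as supportive, with no claim resting on it if the two disagree.

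The cost is wording only: previous falls are already recorded and ward is known. The one practical burden is missing baseline MMSE, which is likely in some confused participants enrolled by proxy consent. Simple imputation, made without regard to arm, is enough for a baseline covariate in a randomised comparison.

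### At least 21 treatment-by-covariate interactions fall under one unadjusted p < 0.05 rule, so about one false subgroup effect is expected if none exists

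*Protocol article*

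**What the plan says.** The Quantitative analysis section first fits a crude Poisson model for bedside falls. It then states that "additional models will adjust for the effects of age, MMSE and mobility/transfer scores", and continues: "Interactions between each of these three variables and treatment group with respect to our primary and secondary outcome measures will also be examined". It ends with a general rule: "A significance level of p < 0.05 will be used for all analyses". No adjustment for multiple interactions is given, no interaction is named as the main one, and the interactions are not called exploratory.

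The outcome section defines a single primary outcome ("The primary outcome measure is the number of bedside in-patient falls per 1,000 bed days") and lists secondary outcomes a to g. Items a to f are quantitative: injurious falls, length of stay, residential status, Barthel Index, mFES and EQ-5D. Item g concerns the experience of participants and staff, and of it the article says "This sub-study will be reported separately".

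The third of the Secondary research hypotheses reads: "That there are groups of patients in whom the health or economic benefits from the intervention are greatest".

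**The concern.** Hypothesis 3 is a claim that subgroups with greater benefit exist. It names neither the covariate nor the outcome. A significant interaction on any of the three covariates and any of the seven outcomes could be offered in its support, so the relevant error is the chance of at least one false interaction across the whole set. Each test carries its own 5% error, and nothing in the article limits how many of them may be reported as significant.

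What is at stake is the credibility of a subgroup finding. The trial is sized for the overall effect on bedside falls and has little power for differences between subgroups. A nominally significant interaction picked from 21 would therefore be weak evidence, although the article's rule would let it be reported at the same level as any other result.

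**Working it through.** **Inputs from the protocol article**

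- Covariates: 3 (Quantitative analysis).
- Outcomes: 1 primary + 6 quantitative secondary = 7. Item g is left out because it is reported separately.
- Level: 0.05 per test (Quantitative analysis).
- Sample size section: "we anticipate a rate of bedside falls of 8.0 per 1,000 bed days in the control group", mean stay 19 days, 35% reduction, 80% power, alpha 0.05, overdispersion 1.5, 905 per arm. Two-sided testing is assumed, because the article does not state the side.

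**The plan's own figure.** The article states no error rate for the interactions. The figure that can be reproduced is the sample size. The Poisson-regression (Signorini) formula, per arm, is

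n = 1.5 × (1.96 × √4 + 0.842 × √(2 + 2/0.65))² / (μ × (ln 0.65)²) / 2

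With μ = 8.0 × 19/1,000 = 0.152 this gives 899; with μ = 0.151, 905; with μ = 0.15, 911. The stated 905 is reproduced within rounding of μ, so the design inputs are understood.

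**Count.** 3 × 7 = 21 tests. This is a minimum: item d names both transfer/mobility and activities of daily living, and counting them separately gives 3 × 8 = 24.

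**Error if no interaction exists**

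- Expected false positives: 21 × 0.05 = 1.05, whatever the correlation.
- At least one, independent tests: 1 − 0.95²¹ = 0.659.
- With 24 tests: 1 − 0.95²⁴ = 0.708.
- Bedside falls only: 1 − 0.95³ = 0.143.

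**Correlated tests.** The article gives no correlations, so these are assumptions. Each row comes from simulating 21 correlated two-sided normal tests, 200,000 draws per setting, with correlation between covariates from 0 to 0.5.

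| Assumed correlation between outcomes | Chance of at least one false interaction |
|---|---|
| Clustered: 0.4–0.7 between closely related outcomes, mostly 0.1 elsewhere | 53–63% |
| 0.3 between all outcomes | 56–62% |
| 0.5 between all outcomes | 49–54% |
| 0.6 between all outcomes | 45–50% |

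**Power for a real bedside-fall interaction.** Assume two equal halves and a ratio of rate ratios of 0.65; neither comes from the article. The interaction's standard error is then about twice that of the main effect.

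- Main effect at exactly 80% power: z = 1.96 + 0.84 = 2.80, so interaction power is Φ(2.80/2 − 1.96) = Φ(−0.56) = 29%.
- Usual log-rate variance at 905 per arm: SE = √(1.5 × (1/0.152 + 1/0.0988)/905) = 0.166 and z = 0.431/0.166 = 2.59, so power is Φ(2.59/2 − 1.96) = 25%.
- First Holm threshold, 0.05/3 = 0.0167 (z = 2.39): Φ(1.40 − 2.39) = 16% and Φ(1.295 − 2.39) = 14%.
- Joint 3-df test at 5% (critical value 7.81), if only one of three uncorrelated covariates modifies the effect: noncentrality 1.40² = 1.96 or 1.295² = 1.68, giving 19% or 17%. Power is higher if more than one covariate modifies the effect.

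**The case against.** The article says that interactions will be examined, after the main model, and subgroup benefit is only the third secondary hypothesis. Interaction analyses are often read as exploratory, and their labelling is often left to an analysis plan, which is not shown here. Pooling all seven outcomes into one family is also a choice: outcome by outcome the figure is 14%, and most of the 66% comes from secondary outcomes, where unadjusted testing is common. The plan does some things well, since it names its covariates and uses interaction terms rather than separate tests within subgroups.

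Much of this stands, and it limits the point. A missing exploratory label alone would be no finding. The article goes further, however: it fixes one significance level for all analyses and states subgroup benefit as a hypothesis. An analysis plan that handled the interactions differently would have to depart from that sentence.

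Four stronger readings are tempting and are not supported:

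- A reader might infer that a false subgroup effect is more likely than not in every case. That depends on correlations the article does not give; if all seven outcomes are highly correlated, the chance falls just below 50%.
- A reader might infer that one p < 0.05 among the 21 settles hypothesis 3. No sentence says so. A general significance level is not a rule for combining tests.
- A reader might infer that the subgroup result decides which patients would get sensors. The article does not say this. Its Health economic analysis section ties national roll-out to incremental cost, incremental cost-effectiveness and their uncertainty.
- A reader might infer that the main result is compromised. The single comparison of bedside-fall rates keeps its own error rate.

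**Conclusion.** The concern holds in a limited form. At least 21 interaction tests come under an unadjusted 5% level in support of a stated hypothesis. If no interaction exists, about one false positive is expected. The chance of at least one is 66% under independence and about 53–63% under the assumed clustered correlations, which are low to moderate. Correlation as high as 0.5–0.6 between all outcomes is unlikely for measures as different as fall counts, length of stay, discharge residence and EQ-5D, and even then the chance stays at about 45–54%. These figures assume that no interaction exists on any outcome. This is worth correcting because it changes what the trial may claim about subgroups; it does not touch the primary conclusion.

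**What to change.** Exempt the interaction analyses from the general p < 0.05 sentence. Test hypothesis 3 formally on the bedside-fall rate only, preferably with one joint 3-df test of the three interactions at 5%. Report the interactions on the six secondary outcomes as exploratory estimates with 95% confidence intervals and no significance claim. Three Holm-adjusted tests on bedside falls are an alternative that names the covariate responsible, but at the first threshold they cut power for a single interaction from about 25–29% to about 14–16%. Labelling all the interactions exploratory would also be acceptable.

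The change is one of wording and loses no planned data or estimate. Its cost is that the other health benefits covered by hypothesis 3, such as mobility, fear of falling and quality of life, would be described by subgroup and not formally tested. It does not cure the low power: the joint test has only about 17–19% if a single covariate modifies the effect, under the assumptions shown. A non-significant result should therefore not be reported as evidence that the effect is the same in all patients.
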